### Statistical Analysis

The CANDLE-AF trial will use an intention-to-treat analysis that includes all participants according to randomization. It is hypothesized that, regarding the AF-detection rate, the 72-h single-patch monitoring will be superior to standard care and non-inferior to the event-recorder type of monitoring. For the baseline variables, bivariate relationships will be investigated using chi-square or Fisher's exact tests and Student's *t*-tests or Wilcoxon rank sum tests. All continuous variables will be represented as mean or median with standard deviation or interquartile range, respectively. And according to the results of the normality test performed by the Shapiro-Wilk test, the *t*-test is performed for data following the normal distribution, otherwise the Mann-Whitney U test will be performed. Categorical and dichotomized variables will be described as percentages and analyzed using Fisher's exact test.

The primary outcome will be compared between the 72-h monitoring group and each control arm using the chi-square test or Fisher's exact tests. Unadjusted outcome effect sizes will be estimated as odds ratios with 95% confidence intervals as appropriate. In addition, for the time to the first documented AF episode during the 12-month observation period, Kaplan–Meier curves will be calculated for each arm and compared using a log-rank test. Moreover, we will compare the total major adverse cardiovascular or cerebrovascular events and the rate of change from antiplatelet to anticoagulant therapy following AF detection, as well as the incidence of recurrent strokes. All analyses will evaluate the effectiveness through multivariate analysis, taking other factors into account in a progressive model. In multivariate analysis, age, hypertension, heart failure, valvular disease, history of myocardial infarction, thyroid insufficiency, obesity, chronic obstructive pulmonary disease, chronic kidney disease, and smoking, which are known independent risk factors for Afib (22–27), are planned to be used as covariate. The Statistical Package for the Social Sciences (SPSS version 26.0, IBM SPSS Statistics, Armonk, New York, USA) will be used for statistical analyses. *P* < 0.05 will be considered statistically significant.

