### Study Duration, Interim Analyses, and Early Termination

The difference in the detection rate of AF is the primary outcome. The device-based monitoring will be stopped when AF is detected. The secondary outcome is the rate of changes from antiplatelet to anticoagulant, major adverse cardiac and cerebrovascular events (composite of nonfatal stroke, nonfatal myocardial infarction, and cardiovascular death), and occurrence of major bleeding (fatal or overt bleeding with a drop in hemoglobin level of at least 2 g/dL or requiring transfusion of at least 2 units packed blood cells, or critical anatomical site hemorrhage (e.g., intracranial, retroperitoneal) within 1 year. For secondary outcome, the follow-up period is 12 months. Changes in antiplatelet and anticoagulant therapy will not affect clinical study discontinuation. Monitoring and follow-up will be terminated early if a skin disease occurs due to the patch, if the patient no longer wants to participate, or if it is impossible for the patient to participate due to causes, such as hospitalization due to a serious disease or death. When discontinuation or drop-out occurs, all data of the participants that were recorded up to that time point will be used, and patient data up to the point of interruption in the intention-to-treat strategy will be used for statistical analysis. If the participant does not want their data to be used, all of their data will be discarded and not used in the statistical analysis.

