### Sample-Size Estimates

The sample-size calculation is based on the primary endpoint: “the detection probability for each group.” The detection probability was assumed as standard treatment: 2.5%, smartphone recorder: 8.5%, single-lead device: 14.5%, based on the SPOT-AF trial (13) and a previous assessment of a simulation in the CRYSTAL-AF trial (18). Non-inferiority margin was assumed to be 2.3% conservatively based on the difference in expected detection rates between single-lead device (14.5%) and smartphone-based device (8.5%) (13, 18). First, for determining the single-lead device's superiority to standard strategy at a significance level (alpha) of 5%, power (1-beta) of 80%, and margin of 2.3%, we calculated that 108 participants are needed in each group, assuming a 10% drop-out rate. 2, to prove the single-lead monitor's non-inferiority to the event recorder with a significance level (alpha) of 5%, power (1-beta) of 80%, and margin of 2.3%, each group needs 200 patients with a 10% drop-out rate. For randomization, each group will recruit 200 participants by applying the results of the pair with the greater number of participants (Figure 1). The sample-size calculation was performed using the Power and Sample Size website (http://powerandsamplesize.com/Calculators/Compare-2-Proportions/2-Sample-Non-Inferiority-or-Superiority, accessed November 22, 2021). Because it is an intention-to-treat study, we plan to conduct analyzes including drop-out cases except which the subject wants to remove the data.

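### The stated primary analysis (chi-square or Fisher's exact test with odds ratios) tests equality and does not apply the 2.3-point non-inferiority margin on which the trial is sized

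*Protocol article*

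**What the plan says.** All places are in the protocol article.

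- **Hypotheses (Statistical Analysis).** The trial is to show that "the 72-h single-patch monitoring will be superior to standard care and non-inferior to the event-recorder type of monitoring". Trial Design and Primary Objectives name the same two questions.
- **Outcome (Study Duration, Interim Analyses, and Early Termination).** "The difference in the detection rate of AF is the primary outcome".
- **Sizing (Sample-Size Estimates).** Assumed detection is 2.5% (standard), 8.5% (event recorder) and 14.5% (patch). The non-inferiority margin is 2.3%, alpha 5% and power 80%, giving 200 per group with 10% drop-out. The other comparison is sized for "superiority to standard strategy at a significance level (alpha) of 5%, power (1-beta) of 80%, and margin of 2.3" percent, giving 108 per group. The larger figure is adopted.
- **Test (Statistical Analysis).** "The primary outcome will be compared between the 72-h monitoring group and each control arm using the chi-square test" or Fisher's exact test.
- **Effect measure (Statistical Analysis).** "Unadjusted outcome effect sizes will be estimated as odds ratios with 95% confidence intervals as appropriate".
- **Decision threshold (Statistical Analysis).** P "< 0.05 will be considered statistically significant".

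The Statistical Analysis section repeats the non-inferiority hypothesis. It does not mention the margin, an interval for the difference in detection rates, or a rule for declaring non-inferiority. The Kaplan-Meier, log-rank and multivariate analyses do not use the margin either.

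**The concern.** The non-inferiority comparison sets the size of the trial, but the analysis named for it belongs to a different hypothesis. Non-inferiority needs the null that the patch detects at least 2.3 points less than the event recorder. Chi-square and Fisher's exact tests have the null that the two rates are equal.

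The effect measure is also on another scale. The outcome and the margin are differences in rates, and the reported measure is an odds ratio. A 2.3-point deficit has no fixed odds-ratio equivalent, because it depends on the comparator's rate.

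Followed literally, the plan can support non-inferiority only when the patch is significantly better. In every other case the rule would have to be supplied later, in an open-label trial, possibly after results are known.

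**Working it through.** **Inputs.** Rates 14.5%, 8.5% and 2.5%, margin 2.3%, alpha 5%, power 80% and 10% drop-out, all from Sample-Size Estimates. Neither the scale of the margin nor the sidedness of alpha is stated there.

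**Step 1: reproduce the plan's sample sizes.** For an absolute margin with unpooled variance,

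n = (z_alpha + z_power)² × [pA(1 - pA) + pB(1 - pB)] / (pA - pB - d)², where d = -0.023 for non-inferiority and +0.023 for superiority by a margin.

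- Variance term, patch v event recorder: 0.145 × 0.855 + 0.085 × 0.915 = 0.20175.
- Non-inferiority, one-sided 5%: (1.645 + 0.842)² × 0.20175 / 0.083² = 181.1, so 182. With drop-out, 182 × 1.1 = 200.2 (182 / 0.9 gives 203). This matches 200.
- Non-inferiority, one-sided 2.5%: 229.9, so 230, or 256 with drop-out (230 / 0.9). This does not match.
- Superiority by 2.3 points, one-sided 5%: variance term 0.145 × 0.855 + 0.025 × 0.975 = 0.14835, denominator 0.097², giving 97.5, so 98. Then 98 × 1.1 = 108. This matches.

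The plan's figures therefore imply an absolute margin of 2.3 percentage points at one-sided 5%.

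**Step 2: power of each analysis, patch v event recorder, at the planned rates.** Non-inferiority power is Φ(0.083 / SE - z_alpha), with SE = √(0.20175 / n), that is 0.03348 for n = 180 and 0.03176 for n = 200. For n = 180, 0.083 / 0.03348 = 2.479, and Φ(2.479 - 1.645) = 79.8%.

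| Analysis | 180 per arm | 200 per arm |
|---|---|---|
| Margin test, one-sided 5% (90% CI) | 79.8% | 83.4% |
| Margin test, one-sided 2.5% (95% CI) | 69.8% | 74.3% |
| Chi-square as written, two-sided 5% | 43.0% | 46.8% |

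The last row is the chance of a significant result in the patch's favour, the only result of the written test that implies non-inferiority.

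**Step 3: two possible results with 200 per arm** (patch v event recorder; Wald intervals for the risk difference).

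| | 29 v 17 (the planned rates) | 10 v 17 |
|---|---|---|
| Chi-square p | 0.060 | 0.16 |
| Fisher p | 0.084 | 0.23 |
| Odds ratio (95% CI) | 1.83 (0.97 to 3.44) | 0.57 (0.25 to 1.27) |
| Risk difference, points | +6.0 | -3.5 |
| 90% CI | 0.8 to 11.2 | -7.6 to 0.6 |
| 95% CI | -0.2 to 12.2 | -8.4 to 1.4 |
| Lower limit above -2.3? | Yes, at both levels | No, at both levels |

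The written test returns the same verdict, not significant, for both.

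**Step 4: the margin as an odds ratio.** With comparator rate p and q = p - 0.023, the odds ratio at the margin is [q / (1 - q)] / [p / (1 - p)]. It is 0.53 at p = 5%, 0.71 at 8.5%, 0.79 at 12% and 0.82 at 14.5%. The odds-ratio interval therefore cannot be compared with one fixed limit.

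**The case against.** The strongest defence is that the parts of a non-inferiority rule are all in the article: an outcome defined as a difference in detection rates, a margin, an alpha, a named non-inferiority sample-size calculator and the hypothesis itself. On this view only a joining sentence is missing, and an analysis plan could supply it. The first half is true. The second would succeed if the article were silent on the test, but it names one for each control arm, and an analysis plan that follows it inherits the mismatch.

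Several stronger readings are tempting, and the document does not support them.

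- *No non-inferiority conclusion is possible.* Too strong. A significant result favouring the patch implies non-inferiority, and the collected data would allow the right interval to be computed.
- *The plan treats a non-significant result as non-inferiority.* No sentence says so. That is a misreading the wording leaves open.
- *Drop-outs are counted as AF-free, and poor adherence to twice-daily recording makes non-inferiority easier to show.* The article says "Because it is an intention-to-treat study, we plan to conduct analyzes including drop-out cases" and that data up to interruption are used. It gives no rule coding drop-outs as AF-free, and participants who withdraw their data are removed. Non-adherence is not drop-out, and loss in the patch arm, for example from skin disease, would push the other way.
- *Non-inferiority must also hold per protocol.* This is debatable. The trial compares monitoring strategies whose convenience is part of the rationale. Device monitoring stops once AF is detected, so a wear or transmission threshold could exclude early detections.
- *The superiority margin must be deleted.* It has little practical effect. The 108 does not bind, and at 200 per arm and the planned rates power is about 97% against the 2.3-point margin (one-sided 5%) and about 99% against zero (two-sided 5%). The article needs only to say which is tested.

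**Conclusion.** The point holds and should be corrected before outcome data are analysed. The test and effect measure named for patch v event recorder do not implement the margin that determines the sample size. At the planned rates, a comparison designed for 80% power would reach a usable conclusion only about 43% to 47% of the time, and the remaining results would be uninterpretable for non-inferiority.

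This rests on two assumptions. The margin is taken as absolute and alpha as one-sided 5%; neither is labelled, but together they reproduce both 200 and 108. The power figures take the planned 14.5% and 8.5% as true and use normal approximations. The mismatch of hypotheses depends on neither assumption.

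**What to change.** In Statistical Analysis:

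1. For patch v event recorder, make the primary analysis the risk difference (patch minus event recorder) in 12-month AF detection with a score or Newcombe confidence interval. Declare non-inferiority if the lower limit lies above -2.3 percentage points.
2. State the confidence level. A 90% interval (one-sided 5%) matches the stated sample size, with power of about 80% at 180 evaluable per arm and 83% at 200. If a 95% interval is chosen, restate the power as about 70% to 74%; keeping 80% would need 230 evaluable, or 256 per group with 10% drop-out.
3. Report the risk difference for patch v standard care too, and say whether superiority is tested against zero or against the 2.3-point margin.
4. Keep the odds ratio as supplementary.

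In Sample-Size Estimates, label the margin as absolute percentage points and give the sidedness of alpha.

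A per-protocol analysis may be added as a sensitivity analysis, not as a condition of the claim.

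No new data are needed. With a 90% interval the cost is wording alone. With a 95% interval it is either lower stated power or more participants.

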### Study Population and Randomization

Seven tertiary hospitals with stroke units in South Korea will participate in this trial and these centers represent a full coverage of all levels of care, including state-of-art tests, monitoring, imaging equipment, the latest treatment policies of specialists, and intensive care units. All patients who first visit the department of neurology with a stroke or TIA without history of AF at the time of admission and if no AF was detected during monitoring of the hospital stay will be enrolled in this study after obtaining voluntary informed consent. In this study, by referring to the inclusion criteria used in CRYSTAL-AF (16), the minimum symptoms required for inclusion by TIA were established: speech or language deficit, weakness of an arm or leg, or hemianopsia. As an inclusion criterion, history of AF was established as a person who did not have AF at the time of admission and who had no prior AF diagnosis. A surface ECG at hospitalization will be used as the screening test to check for pre-existing AF. During the hospital stay, continuous ECG monitoring will be performed through telemonitoring. Before being discharged, all enrolled participants will be randomized to the: 1) the standard treatment group, 2) the single-lead ECG patch group, and 3) the event-recorder group. The exclusion criteria are described in Figure 1. We performed block randomization using random number generator function of Excel (Microsoft, USA). The randomization ratio is 1:1:1.

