Recurrent TIA or ischemic stroke in 3 years showed no significant difference in the standard group and ILR group (9% vs. 11%, total *n* = 441; *p* = 0.64) (5, 6). The Find-AF-randomized trial demonstrated no significant difference in recurrent stroke at 12 months in subclinical AF patients of 10-day Holter monitoring group and control group (3.7% in 200 patients vs. 5.4% in 198 patients; *p* = 0.46) (21). As such, there have been several attempts to elucidate the relationship between the more sensitive detection of silent AF after cryptogenic stroke and the prognosis, but there were no results showing a clear difference.

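### Unadjusted tests and a ten-covariate model with 3 to 4 expected events per coefficient are both planned for the primary outcome, and the plan does not say which decides

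*Protocol article*

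**What the plan says.** All places are in the protocol article.

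- **Statistical Analysis, unadjusted part.** The primary outcome in the patch arm is compared with each control arm by chi-square or Fisher's exact test. Effect sizes are unadjusted odds ratios with 95% confidence intervals. Time to first AF is compared by Kaplan–Meier curves and a log-rank test.
- **Statistical Analysis, adjusted part.** After listing major cardiovascular and cerebrovascular events (MACCE), the switch to anticoagulation and recurrent stroke, the section states: "All analyses will evaluate the effectiveness through multivariate analysis, taking other factors into account in a progressive model". The covariates are "age, hypertension, heart failure, valvular disease, history of myocardial infarction, thyroid insufficiency, obesity, chronic obstructive pulmonary disease, chronic kidney disease, and smoking".
- **Clinical Monitoring.** Sex, age, blood and biochemical results, myocardial enzymes, echocardiography and brain imaging are to be recorded and used as covariates for primary or secondary outcomes. Most of these, sex among them, are not on the list of ten.
- **Sample-Size Estimates.** "The detection probability was assumed as standard treatment: 2.5%, smartphone recorder: 8.5%, single-lead device: 14.5" (percent), with the non-inferiority margin set at 2.3 percentage points. The final size is fixed by "each group will recruit 200 participants by applying the results of the pair with the greater number of participants".

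**The concern.** Two matters meet here.

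First, an unadjusted and an adjusted analysis of the primary outcome stand side by side, the second worded to cover all analyses, with no statement of which governs. With two covariate pools and undefined model steps, several estimates of the same primary effect could be produced in an open-label trial, and the text does not rank them.

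Second, the adjusted model is too large for the events expected. With few events per coefficient, maximum-likelihood logistic regression tends to push odds ratios away from 1. A rare covariate with no events among its carriers has no finite coefficient (separation). If the adjusted odds ratio were taken as the main result, the patch's advantage over standard care would be overstated. It would also not test the non-inferiority margin directly, because that margin is a difference in detection proportions.

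**Working it through.** **1. Reproduce the plan's sample sizes.** Inputs are the rates and margin in Sample-Size Estimates. Formula: n = [p1(1−p1) + p2(1−p2)] × (z₁₋α + z₀.₈)² / (distance from margin)², with one-sided α = 5%, so (1.645 + 0.842)² ≈ 6.183.

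- Superiority, 14.5% vs 2.5%, margin 2.3 points: (0.1240 + 0.0244) × 6.183 / (0.120 − 0.023)² = 97.5. Times 1.1 gives 107.2, so 108. The plan: "we calculated that 108 participants are needed in each group, assuming a 10% drop-out rate".
- Non-inferiority, 14.5% vs 8.5%: (0.1240 + 0.0778) × 6.183 / (0.060 + 0.023)² = 181.1. Times 1.1 gives 199.2, so 200. The plan: "significance level (alpha) of 5%, power (1-beta) of 80%, and margin of 2.3%, each group needs 200 patients with a 10% drop-out rate".

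Both figures reproduce, so the trial was sized on an unadjusted difference between two proportions.

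**2. Expected AF cases.** "The randomization ratio is 1:1:1", with 200 per arm:

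- patch: 200 × 0.145 = 29
- standard: 200 × 0.025 = 5
- event recorder: 200 × 0.085 = 17

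**3. Events per coefficient.** Ten covariates at one coefficient each, plus one treatment term (two arms) or two (three arms), intercept not counted. Coding smoking or obesity in several categories would lower these figures.

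| Model | Events at 200/arm | Coefficients | Per coefficient | At 180/arm (10% lost) |
|---|---|---|---|---|
| Patch vs standard | 29 + 5 = 34 | 11 | 3.1 | 30.6 / 11 = 2.8 |
| Patch vs event recorder | 29 + 17 = 46 | 11 | 4.2 | 41.4 / 11 = 3.8 |
| Three arms | 51 | 12 | 4.25 | 45.9 / 12 = 3.8 |

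**4. Recurrent stroke.** The plan gives no rate of its own. The Discussion cites one 12-month trial with "3.7% in 200 patients vs. 5.4% in 198 patients". If those rates applied, a pair of arms would have 400 × 0.037 = 14.8 to 400 × 0.054 = 21.6 events, about 15–22, or 1.3–2.0 per coefficient.

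**5. Effect on the odds ratio.** Simulation of 4,000 trials per scenario, 200 per arm. Covariate effects (log-odds 0.2 to 0.5) and prevalences are assumptions, because the document gives none. Ranges cover the common-covariate and rare-covariate settings of step 6.

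| | True odds ratio | Median estimate | Geometric mean |
|---|---|---|---|
| Patch vs standard, adjusted | 6.91–6.98 | 7.65–7.67 (10–11% high) | 8.18–8.23 (17–19% high) |
| Patch vs standard, unadjusted | 6.61 | 6.68–6.81 (1–3% high) | 7.16–7.27 (8–10% high) |
| Patch vs event recorder, adjusted | 1.87 | 1.93 (3% high) | 1.94 (4% high) |

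Other covariate assumptions widen the adjusted range to roughly 10–25% for patch vs standard and 2–5% for patch vs event recorder. Coverage of the 95% interval for the adjusted odds ratio was about 0.95–0.98. Firth penalisation brought the patch-vs-standard odds ratio to within about 5% of the truth on the average log-odds scale.

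**6. Failed fits at 200 per arm** (at least one coefficient not converging).

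- Every binary covariate at 15% or more: 0.7% (patch vs standard) and 0.2% (patch vs event recorder).
- Several covariates at 4–8%: 51% and 31%. Other assumptions with rare covariates bring this down to roughly 15%.
- Treatment term undefined because the standard arm has no events: 0.975²⁰⁰ = 0.6%; simulated, under 1%.

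**The case against.** The strongest reply is that the primary analysis is already unadjusted. The section names chi-square or Fisher tests and unadjusted odds ratios for the primary outcome, and the sample size rests on two proportions. That test has about 99% power for 14.5% vs 2.5% at 200 per arm (two-sided 5%, no margin). The natural reading is an unadjusted test first and adjustment second, and an article may leave model steps to a fuller document. Much of this stands. A reader might infer that every effectiveness analysis will be the ten-covariate model, but the named unadjusted tests rule that out. What remains is that the later sentence covers all analyses, Clinical Monitoring extends adjustment to the primary outcome, and neither ranks the results.

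Other stronger readings also lack support:

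- **34 events throughout.** That count belongs to patch vs standard only.
- **The model will often fail.** This depends on prevalences the document does not state, and failures fall mainly on rare-covariate coefficients.
- **Progressive means data-driven selection.** The covariates are named in advance, and the word may mean fixed sequential blocks. The text settles neither.
- **The bias is peculiar to adjustment.** Part of it is ordinary small-sample bias, which the unadjusted odds ratio shares (8–10% in geometric mean, 1–3% in median). The adjusted model adds to it on both scales.

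The Introduction presents the effect on recurrence and MACCE as pilot exploration, so sparse events there matter less.

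**Conclusion.** The concern holds in limited form. The plan fixes a ten-covariate model with 3.1 to 4.25 expected AF cases per coefficient and does not say whether it or the unadjusted test decides each primary comparison. The event counts need only the plan's own rates and 200 per arm.

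The consequence is moderate: an overstatement of roughly 10–25% in the patch-vs-standard odds ratio and 2–5% for patch vs event recorder, both resting on assumed covariate effects. Failed covariate coefficients run from under 1% of fits to about half, according to assumed prevalences. Recurrent stroke would be sparser still if the cited rates applied.

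Nothing here shows that the superiority or non-inferiority conclusion would be wrong. The unadjusted test protects the primary result, provided the plan says that it governs.

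**What to change.** 1. State that the unadjusted comparison of detection proportions decides each of the two primary comparisons. This matches the scale on which the trial was sized and the margin set.
2. Label the multivariable analysis as supportive, and replace the sentence that applies it to all analyses.
3. Fit one supportive model, once, to all three arms. Use either a short covariate list named before the data are seen or, if all ten are kept, Firth-penalised logistic regression.
4. Drop the progressive build, or fix its steps and their order in advance.
5. Reconcile the covariates in Clinical Monitoring with the ten in Statistical Analysis.
6. Apply the same rules to MACCE and recurrent stroke.

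Cost: wording only, with no change to sample size or data collection. The supportive analysis will either carry fewer covariates or need a penalised model that may lie outside the standard procedures of the SPSS package named in the plan.
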